### Random allocation and blinding

After providing their written consent, patients are randomly allocated in a 1:1 ratio to the intervention or control group (A or B). Patients will be randomized through a stratified sequential randomization plan generated online. Randomization will be stratified by disease severity (Acute Physiology and Chronic Health Evaluation (APACHE) II,^1^ 0–35 and 35–70). For allocation concealment, we will use sealed opaque envelopes; inside each there is a carbon paper and the A or B card. To avoid probable selection bias, we will write the patient’s name on the envelope before opening it. All patients, researchers, and medical staff will be blinded to the allocation to either synbiotic or placebo capsules. An available third party, the secretary of the ICU, will be aware of whether A or B is allocated the synbiotic supplement. In the case of any complication associated with the intervention allocated, the medical staff will refer to the secretary for details.

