**Fig. 3 Fig3:**
[figure not shown]
Flow chart of GRV management. Abbreviations: EN, enteral nutrition; GRV, gastric residual volume; ICU, intensive care unit; ml, milliliter; NUTRIC, Nutrition Risk in Critically Ill; SPN, supplementary parenteral nutrition

In the intervention group, patients will receive Lactocare (ZistTakhmir) capsules 500 mg every 12 h for 14 days. Each capsule contains *Lactobacillus casei* 1.5 × 10^9^ colony-forming units (CFU), *Lactobacillus acidophilus* 1.5 × 10^10^ CFU, *Lactobacillus rhamnosus* 3.5 × 10^9^ CFU, *Lactobacillus bulgaricus* 2.5 × 10^8^ CFU, *Bifidobacterium breve* 1 × 10^10^ CFU, *Bifidobacterium longum* 5 × 10^8^ CFU, *Streptococcus thermophilus* 1.5 × 10^8^ CFU, and fructooligosaccharides (FOS). The probiotics capsule will be given through the NGT, separately from gavage, after feeding. Patients in the control group will receive a placebo capsule, which contains only sterile maize starch and is similar to probiotic capsules. The liquid preparations ready for gavage through the NGT are also similar in color and odor.

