### Description of evaluations

As shown in Fig. 2, calorie achievement goals are set according to the patients’ modified NUTRIC score. In everyday visits, we will evaluate GI signs and symptoms (e.g. vomiting, diarrhea, abdominal distention) and gastric residual volume (GRV). If there is no sign or symptom of intolerance and GRV is less than 250 ml, EN will be increased by 10%. Otherwise, we will approach as shown in Fig. 3. Energy homeostasis (calorie intake-estimated calorie requirement) will be recorded each day. Mid-arm circumference, which is an available anthropometric measurement tool, will be evaluated twice a week. As all patients receiving EN should be monitored for some clinical and laboratory variables, we set our monitoring approach as reported by Berger MM, et al. [34], Monitoring nutrition in the ICU, Clinical Nutrition (2018). Concomitant medications, pressure ulcers, infectious complications, and other adverse events will be recorded every day. The APACHE II and Sequential Organ Failure Assessment (SOFA) will be scored on days 0, 8, and 15. Before and after the intervention, fasting blood and 24-h urine samples will be obtained. Urine urea nitrogen, 3-Methyl histidine, and creatinine will be measured in urine samples. Fasting blood glucose, insulin, C-reactive protein (CRP) and endotoxins will be measured in fasting blood samples.

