## Statistical considerations

### General design issues

Data will be analyzed using the intention-to-treat approach.

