### Sample size and randomization

We did not find any similar study that has evaluated our primary objectives. So, we considered one of the main secondary objectives to estimate the required sample size. Mahmoodpoor and co-workers [35] reported the ICU stay in two study groups as 18.6 ± 8 and 11.6 ± 6.3 days. Considering alpha error of 0.05 and power of 80%, the required sample size allowing for 10% dropout is 20 patients in each group.

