### Data analysis

Data will be analyzed using SPSS for windows version 11.5 and MedCalc Statistical Software version 18.11.3 (MedCalc Software bvba, Ostend, Belgium; https://www.medcalc.org; 2019). Descriptive (frequency, percentage, mean, standard deviation) and inferential analysis (student *t* test, paired sample *t* test, repeated measures analysis of variance (ANOVA)) will be performed. Any covariates will be controlled by ANCOVA or binary logistic regression. All tests will be two-tailed and a *p* value <0.05 will be considered as statistically significant.

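### Six of the eight primary outcomes, plus insulin, rest on a single day-15 sample with none described for patients who leave the ICU or die earlier, and on the plan's own ICU-stay figures the resulting loss is unequal between arms and above the 10% allowed

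*Protocol article*

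**What the plan says.** All references are to the protocol article.

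- **Sampling.** Description of evaluations: "Before and after the intervention, fasting blood and 24-h urine samples will be obtained". In Table 1 the rows for outcomes and for insulin are marked only before the intervention and in the day-15 close-out column. Energy balance and glucose are marked daily. No section describes a set taken at ICU discharge, on the ward or at an early end of treatment.
- **Course.** Interventions, administration, and duration: "capsules 500 mg every 12 h for 14 days". A completed course therefore ends the day before the close-out column.
- **Analysis set.** General design issues: "Data will be analyzed using the intention-to-treat approach".
- **Sizing.** Sample size and randomization cites an earlier study that "reported the ICU stay in two study groups as 18.6 ± 8 and 11.6 ± 6.3 days", and concludes: "Considering alpha error of 0.05 and power of 80%, the required sample size allowing for 10% dropout is 20 patients in each group". It does not say which stay belongs to which group.
- **Entry.** Inclusion criteria require an expected ICU stay above 14 days. Exclusion criteria remove patients expected to stay under 4 days. Patients enter 24–48 h after admission.
- **Expected effect.** The Discussion expects the intervention to shorten ICU stay.

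**The concern.** An outcome measured once after treatment exists only for patients who can be sampled on that day. Here the day is fixed, while the stay assumed for sizing is in one group shorter on average than the course itself. The sampled patients would then be mainly the longer stayers, and the degree of selection would differ by arm because stay is something the product is meant to change. Randomisation no longer protects that comparison, and no later analysis plan can recover a sample that was never taken. The urinary muscle-breakdown markers, which carry the muscle-wasting part of the primary objective, are all affected.

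**Working it through.** **1. Which outcomes are affected.** Of the eight primary outcomes, energy homeostasis is recorded daily. Glucose homeostasis is half covered, since glucose is daily and insulin is not. That leaves nitrogen balance, 3MH, 3MH/creatinine, glycerol, CRP/NLR and endotoxin: six outcomes, plus insulin. Glycerol and NLR are not named in Description of evaluations and have no row of their own in Table 1. I take them to fall under its outcomes row.

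**2. The plan's own figure.** Two-sided alpha 0.05 ("All tests will be two-tailed"), power 80%, 1:1 allocation. Pooled SD = √((8² + 6.3²)/2) = 7.20. Standardised difference = (18.6 − 11.6)/7.20 = 0.972. The t-test needs 17.6, so 18 per arm, and 18/0.9 = 20. The stated 20 per group reproduces, so these stays and the 10% are the working assumptions of the plan.

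**3. Share out of the ICU before the sample.** For cut-off c, the share is F(c), where F has the stated mean and SD. The shape of F is not given, so I use normal, gamma and lognormal. If stay is counted from admission and the study starts 1–2 days later, study day 15 is about ICU day 16–17. I also show c = 15, as if study day and ICU day coincided. Normal example at c = 15: Φ((15 − 18.6)/8) = 0.326 and Φ((15 − 11.6)/6.3) = 0.705.

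| c (ICU day) | Shape | 18.6-day arm | 11.6-day arm | Overall |
|---|---|---|---|---|
| 15 | normal | 0.326 | 0.705 | 0.516 |
| 15 | gamma | 0.368 | 0.749 | 0.559 |
| 15 | lognormal | 0.376 | 0.776 | 0.576 |
| 16 | normal | 0.373 | 0.758 | 0.565 |
| 16 | gamma | 0.422 | 0.789 | 0.606 |
| 16 | lognormal | 0.437 | 0.812 | 0.625 |
| 17 | normal | 0.421 | 0.804 | 0.613 |
| 17 | gamma | 0.476 | 0.823 | 0.649 |
| 17 | lognormal | 0.495 | 0.843 | 0.669 |

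The range is 33–50% against 70–84%, or 52–67% overall, with a gap between arms of 35–40 percentage points. Of 20 per arm, about 10–13.5 and 3–6 would remain.

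**4. If the entry estimate were perfect.** Suppose every enrolled patient truly stays more than 14 days. The share lost is then [F(c) − F(14)]/[1 − F(14)].

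| c | 18.6-day arm | 11.6-day arm | Overall |
|---|---|---|---|
| 15 | 0.061–0.090 | 0.153–0.162 | 0.111–0.125 |
| 16 | 0.125–0.178 | 0.286–0.310 | 0.218–0.237 |
| 17 | 0.193–0.264 | 0.402–0.443 | 0.318–0.337 |

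The range is 6–26% against 15–44%, or 11–34% overall. Of 20 per arm, about 14.7–18.8 and 11.1–16.9 would remain (20 × (1 − share)). In this case no stay is below 14 days, so a mean of 11.6 days cannot describe the trial population and the sizing loses its basis.

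**5. Comparison with the allowance.** Overall loss exceeds 10% in both cases: by a wide margin on the stated stays, and only just at the most favourable corner of the second table (11%).

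**The case against.** The best defence is the entry rule. It exists to match patients to a 14-day course, and with good clinical estimates most patients would still be in the ICU. This has force: a reader might infer from the stay figures alone that most patients will be lost, and the plan does not support that without qualification. The truth probably lies between the two tables. The rule does not remove the problem, because an estimate made at entry is imperfect and a stay just over 14 days from admission still ends before ICU day 16–17.

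The sampling sentence can also be read as each patient's own end of treatment, and leaving the ICU is not leaving the hospital: hospital stay and 28-day mortality are outcomes, and blood and urine can be collected on a ward. A condensed article may omit such detail. But Table 1 names day 15 and nothing in the text provides for anything else, so if the intention differs, the schedule should say so.

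Four further inferences go beyond the documents:

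- That seven of the eight primary outcomes are affected. Daily glucose makes it six plus insulin.
- That an intention-to-treat comparison is impossible. Large, unequal missingness compromises it but does not rule it out, and missing-data methods may sit in an analysis plan not shown.
- That the bias must run against the synbiotic. Remaining synbiotic patients may be the slower recoverers, but early deaths remove the sickest patients and act the other way.
- That the lost power or the bias can be stated as a figure. The 0.972 SD effect belongs to ICU stay, and the plan says no similar study had evaluated its primary objectives. Any correlation between a marker and length of stay would be my assumption.

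**Conclusion.** The point holds. Six primary outcomes and insulin depend on one day-15 sample, and no provision is described for patients gone by then. On the stays used for sizing, 52–67% would be out of the ICU (70–84% against 33–50%). With a perfect entry estimate, 11–34% would be (15–44% against 6–26%). Either way the overall loss exceeds the 10% allowed and is unequal between arms. The missingness depends on ICU stay, which the product is expected to change, so the intention-to-treat comparison of these outcomes is seriously compromised. The direction of bias is uncertain.

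This rests on four assumptions: the three distribution shapes; a start 0–2 days after admission; no sampling after ICU discharge; and the 11.6-day figure being the synbiotic arm, which I infer from the expected benefit. The overall figures do not depend on the last of these.

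**What to change.** 1. **Patients still to be sampled.** Take the single post-treatment set at day 15, or at the end of ICU stay if earlier, or on the ward at day 15 where the patient is still in hospital. Record the sampling day and report results by sampling day as a sensitivity analysis. This adds no samples per patient. The cost is that exit samples follow shorter exposure and come earlier in the shorter-stay arm, so timing itself can differ by arm. A short-notice discharge may also not allow the meat-free day before the urine collection. Deaths before the sample remain missing and should be counted by arm.
2. **Sizing text.** Reconcile the 10% dropout figure with the ICU-stay figures and the entry criterion of more than 14 days, and restate the number expected to be sampled for these outcomes. This is a wording change.
3. **Patients already past the fixed day-15 schedule.** Trial status gives a recruitment start of March 2019 and a protocol version of January 2020, so there are probably many, and they cannot be re-sampled. Report numbers sampled by arm with reasons (discharge, death), and describe the result as a comparison among patients still available at day 15, not as intention-to-treat. This costs nothing beyond a more modest claim.

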## Safety assessment

Despite the ample evidence supporting the safety of probiotics in critically ill patients, there are case reports of risks and suggested theoretical risks related to probiotic administration. The most important is the risk of bacteremia and fungemia in high-risk populations, which may be associated with improper use and unintended contamination of central-line catheters [33]. To avoid risk of bacteremia we will not include a high-risk population, such as patients who have recently had major surgery, or patients with short bowel syndrome, heart valve disease, artificial heart valve, or patients who are immunocompromised. We will also pay careful attention to the proper administration and handwashing protocols. Gene transfer and over-stimulation of the immune system are other suggested theoretical risks, on which there is not yet any evidence in humans [33].

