## Selection and enrollment of participants

### Inclusion criteria

Participants must meet all the inclusion criteria to participate in this study: adults aged 18–65 years; admitted to the ICU; hemodynamically stable within 24–48 h after admission; requiring exclusive enteral nutrition (EN) via a nasogastric tube (NGT); not taking any kind of microbial cell preparations (prebiotics probiotics, synbiotics); estimated length of ICU stay more than 14 days; and provision of written consent.

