### Exclusion criteria

All candidates meeting any of the exclusion criteria at baseline will be excluded from study participation: pregnancy or lactation; any contraindication to EN; any contraindication to insertion of the NGT; receiving immunosuppressive treatment, radiotherapy, or chemotherapy; hematologic disease; acquired immune deficiency syndrome (AIDS); transplant recipient; known allergy to microbial cell preparations; cancer or autoimmune diseases; artificial heart valve or congenital heart valve disease; estimated length of ICU stay less than 4 days; gastric disease; or gastrointestinal tract (GI) tract surgery.

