## Trial status

Recruitment was started on 1 March 2019 and is estimated to be completed by October 2019. Recruitment was ongoing at the time of submission. This is the last protocol version (Number 5, 15 January 2020).

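### The safety section rules out recent major surgery and heart valve disease, but the exclusion criteria bar only GI tract surgery and artificial or congenital valve disease

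*Protocol article*

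**What the plan says.** The Safety assessment section describes the product's risks and how the trial will limit them. To avoid bacteraemia, it says the trial "will not include a high-risk population, such as patients who have recently had major surgery, or patients with short bowel syndrome, heart valve disease". It then adds patients with an artificial valve and patients who are immunocompromised. Its other precautions are careful administration and handwashing.

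The Exclusion criteria give the rule by which candidates are turned away: "All candidates meeting any of the exclusion criteria at baseline will be excluded from study participation". On valves, the criterion reads "artificial heart valve or congenital heart valve disease". On surgery, the list ends with "gastric disease; or gastrointestinal tract (GI) tract surgery". The remaining criteria include several conditions and treatments that compromise immunity, and any contraindication to enteral nutrition (EN).

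The Inclusion criteria cover age, ICU admission, haemodynamic stability, exclusive EN by nasogastric tube, no current microbial preparations, expected ICU stay and consent. None concerns surgery or valve disease.

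**The concern.** Two current parts of the protocol set different limits on who may be given live bacteria. Of the product's possible harms, the Safety assessment section says: "The most important is the risk of bacteremia and fungemia in high-risk populations". Keeping those populations out is the first precaution it names. If the eligibility list is narrower than the safety statement, patients the protocol regards as high risk can pass screening, and the safety statement no longer describes the people treated.

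Exposure is not trivial. Adding the strain counts given under Interventions, administration, and duration, in units of 10^9 CFU: 1.5 + 15 + 3.5 + 0.25 + 10 + 0.5 + 0.15 = 30.9. That is about 3.1 × 10^10 CFU per capsule, given every 12 h for 14 days (2 × 14 = 28 capsules).

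Daily recording of infections and adverse events can detect harm but does not prevent it. Eligibility screening is where this protection has to work.

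**Working it through.** The plan gives no figure on this point, so the check is a comparison, item by item, of the five groups in the Safety assessment section with the Inclusion and Exclusion criteria.

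| Group the safety section says will not be included | What the eligibility criteria contain | Match |
|---|---|---|
| Artificial heart valve | Listed by name | Full |
| Immune compromise | Eight related entries: immunosuppressive treatment, radiotherapy, chemotherapy, haematologic disease, AIDS, transplant, cancer, autoimmune disease | Largely covered |
| Heart valve disease | Congenital disease only, besides artificial valves | Partial: acquired native valve disease is not barred |
| Recent major surgery | GI tract surgery only | Partial: recent non-GI major surgery is not barred |
| Short bowel syndrome | Not named; reached only through GI tract surgery, contraindication to EN and the exclusive-EN requirement | Indirect |

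The count is 1 full + 1 largely covered + 2 partial + 1 indirect = 5.

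Three readings that might remove the two partial matches were considered:

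1. *The safety section means congenital valve disease only.* It does not say so. It names heart valve disease without qualification and lists the artificial valve separately.
2. *The safety section means GI surgery only.* It refers to major surgery in general, qualified only by its being recent.
3. *Another criterion catches these patients.* None does. A patient aged 18–65 with rheumatic or degenerative native valve disease, or recovering from major orthopaedic, vascular or thoracic surgery, who is stable, tube-fed and expected to stay more than 14 days, can meet every inclusion criterion and no exclusion criterion.

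The mismatch therefore stands for acquired native valve disease and for recent non-GI major surgery.

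**The case against.** The strongest reply is that the protocol should be read as a whole. The Safety assessment section is itself current text and commits the trial not to include these patients; nothing in the eligibility criteria says they may be enrolled. On that reading the defect is an exclusion stated in one place and not repeated in another. This is fair as to intent: the protocol does not plan to dose these patients. It does not make the texts agree, because the exclusion list is not silent on these topics. It addresses both valves and surgery and gives each a narrower scope.

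A second reply is that the article is condensed, and the full protocol or screening form, neither of which is shown, may carry the wider criteria. That is possible, and it is why the consequence is put as what could happen. But both statements are printed, and a fuller document would not reconcile them as they stand.

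Third, the risk may be small. The safety section cites ample evidence of safety in the critically ill and links bacteraemia and fungaemia partly to improper use and catheter contamination, which handwashing and careful administration address. The site is a medical ICU, and half of the 40 planned patients receive placebo. These points bear on how many patients might be harmed, and they stand as far as they go. But the setting is not an eligibility rule, it does nothing for the valve gap, and the Background counts major surgery among the usual reasons patients are in an ICU.

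Finally, naming short bowel syndrome is largely tidying, since it is already reached indirectly. That is accepted.

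**Conclusion.** The concern holds. The exclusion criteria do not carry through the safeguard stated in the safety section: two of its five groups are only partly barred, leaving acquired native valve disease and recent non-GI major surgery open to enrolment when the list is used alone. It is an inconsistency in a safety rule, not evidence that anyone was wrongly enrolled. The number of patients affected is unknown; it cannot exceed the planned 40, of whom 20 would receive the synbiotic, and may well be small or nil. The practical consequence assumes that screening follows the printed exclusion list. The sample size calculation and the analysis are not affected. It should be fixed, because it concerns what the protocol itself ranks as the leading risk and the remedy is cheap.

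**What to change.** Amend the Exclusion criteria, and any screening form built on them, to add:

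- recent major surgery of any type, with a time window that the investigators must set, since the safety section gives none;
- any heart valve disease, congenital or acquired, alongside artificial valves;
- short bowel syndrome, by name.

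The Trial status section says "Recruitment was started on 1 March 2019 and is estimated to be completed by October 2019", that recruitment was still ongoing at submission, and that version 5 is dated 15 January 2020. A changed list protects only patients still to be enrolled. So also check everyone already enrolled against the aligned criteria and report any who fall in these groups. If there are any, narrow the statement in the Safety assessment section so that it describes the population treated.

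The cost is a short amendment, a review of at most 40 records and, if recruitment is still open, possibly a few fewer eligible patients.

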## Intervention discontinuation

If intervention-related side effects exceed the level reported by previous studies, we will stop the intervention and present the results to the Ethics Committee of Mashhad University of Medical Sciences (MUMS) for further decision making. If adverse events are caused by the study intervention, the researcher and medical team will provide timely and proper treatment to participants.

